## Abstract

Background: Age-related changes can lead to dietary insufficiency in older adults. The inclusion of high-quality, nutrient-dense foods such as ruminant milks can significantly improve health outcomes. However, many older adults worldwide do not meet daily milk intake recommendations because of digestive discomfort and health concerns. Ovine and caprine milks are increasingly popular for their perceived digestive and nutritional benefits. While preclinical studies suggest differences in milk digestion, human studies investigating acute postprandial responses remain inconclusive, and the impacts of sustained milk consumption remain uncertain. Objectives: Hence, we present a randomized controlled trial investigating how the sustained consumption of bovine, caprine, or ovine milk influences digestion, nutrition, and metabolism in older women. Methods: A total of 165 healthy older women were randomized to receive bovine, caprine, or ovine milk, or no milk, twice daily for 12 weeks. The primary outcome is the impact of milk consumption on digestive comfort assessed via the Gastrointestinal Syndrome Rating Scale (GSRS). Secondary outcomes include changes in nutrient intake, plasma amino acid and lipid appearance, bowel habits, the gut microbiota, cardiometabolic health, physical function, physical activity, sleep, mood, sensory perception, and emotional response. Conclusions: The findings could inform dietary recommendations for older women and facilitate the development of targeted functional food products.

## 1. Introduction

The world’s population is aging. By 2030, every sixth person in the world will be over the age of 60 [1]. This brings unprecedented public health challenges as increased longevity is not always accompanied by increased health span [2]. In fact, disorders arising in those over the age of 60 account for 23% of the world’s disease burden [3].

Aging is a complex process characterized by molecular, cellular, physiological, and functional changes throughout the body that contribute to age-related declines and disorders [4]. The older population often experiences changes in eating behavior because of reduced appetite, taste and smell alterations, and oro-dental impairments, all of which may contribute to inadequate food intake, poor diet quality and nutritional deficiency [5,6]. This condition, often known as the “anorexia of aging”, is a significant predictor of negative health outcomes such as frailty, falls, and increased morbidity and mortality [5,7]. Lifestyle factors such as diet and nutrition are key modifiable targets for preserving health and preventing or slowing the progression of age-related disorders [2,8].

Most dietary recommendations for the older population focus on the addition of nutrient-dense foods to address key nutritional issues and meet nutrient and caloric needs [6,9]. The nutrient richness of dairy products makes them well-suited for this paradigm. Adults meeting daily dairy recommendations are more likely to have adequate intakes of key nutrients such as protein, calcium, magnesium, zinc, riboflavin, and vitamin B12 [10,11,12,13,14], nutrients that are often low in the older population [15,16,17,18,19]. Despite this, the average adult consumes less than one serving of dairy each day [20], often because of concerns about digestive discomfort, weight gain, and other perceived adverse health effects of dairy consumption [21,22]. Women, in particular, tend to report more gastrointestinal symptoms [23,24,25,26,27], possibly because of an interplay of physiological and psychosocial factors [28,29], and generally consume less milk compared to men [11,21,30]. Older women are also at greater risk for nutrient insufficiency, though reasons for this remain unclear and may include physiological, socioeconomic, and societal factors such as gender inequality and widowhood [31,32,33].

Bovine milk and its derivatives are widely consumed because of their widespread availability and large production volumes [34]. However, changing dietary preferences, cow milk allergy, and lactose intolerance have led to a rising interest in alternative milks [35,36]. Other ruminant milks, such as caprine and ovine milks, are gaining popularity because of the purported health and environmental benefits they have over bovine milk [37,38]. Milk composition can vary considerably within species because of breed, age, season, diet, and lactation stage [39,40]. However, greater compositional, structural and physicochemical differences exist between milks from different species which may impact their digestive behavior and tolerability [34,39,40,41]. For instance, while bovine and caprine milks have similar fat and protein content, ovine milk is notably higher in both macronutrients [42]. Additionally, different proportions of casein and whey, the two major protein fractions in ruminant milks, could impact curd formation in the gastric environment and influence protein hydrolysis rates and digestive behavior [37,40,43,44]. Furthermore, the breakdown and absorption of milk fats in the stomach and small intestine may also be influenced by differences in fatty acid composition and milk fat globule size between species [34,45,46,47].

In vitro studies exploring the digestive dynamics of different ruminant milks [48,49,50], and human trials focusing on acute responses to consuming these milks [51,52,53,54,55] suggest potential differences in digestive behavior. However, there is a paucity of well-controlled trials, particularly in the older population, to understand the long-term effects of consuming different ruminant milks. Therefore, we designed the effects of daily consumption of ruminant milk on digestive comfort and nutrition in older women (YUMMI) study to address this research gap by evaluating the effects of consuming ruminant milks (i.e., bovine, caprine, or ovine) on digestive comfort, nutrition and metabolism in older New Zealand women over 12 weeks. We hypothesize that different milks may have different impacts on digestive comfort and that the addition of ruminant milks, regardless of species, could improve nutrient intake in older women.

The primary aim of the study is to determine the effects of 12-week ruminant milk consumption on digestive comfort of older women using the Gastrointestinal Syndrome Rating Scale (GSRS). The key secondary aim is to determine the effects of 12-week ruminant milk consumption on nutrient intake of older women based on biomarkers of nutrient status (amino acids and trace elements concentrations) and self-reported dietary data (protein intake). Exploratory outcomes include evaluating the effects of 12-week ruminant milk consumption on bowel habits (bowel movement diary), cardiometabolic health (blood lipids, hemoglobin A1c (HbA1c), body weight, body composition, blood pressure), physical function (timed walk test, handgrip strength test), physical activity (accelerometry), and sleep (accelerometry and Leeds Sleep Evaluation Questionnaire), mood (Patient-Reported Outcomes Measurement Information System (PROMIS): Anxiety, Depression), sensory and emotional responses (sensory and emotional assessments), and the composition and predictive function of the gut microbiota (metagenomic sequencing of stool samples).

In addition to the 12-week intervention described above, we also incorporated an investigation to determine the acute effects of consuming a bolus dose of ruminant milk on digestive comfort (appetite and satiety questionnaire), digestive function (amino acid appearance), and acute cardiometabolic effects (GlucoTRIG index [56]). This investigation was conducted both at baseline and again after the 12-week intervention in a sub-group of participants to study potential adaptations to nutrient metabolism with regular milk intake.

## 2. Materials and Methods

### 2.1. Study Design and Setting

The YUMMI study is a 12-week multi-arm, parallel, multi-center, single blinded randomized controlled trial carried out at the Dunedin and Christchurch campuses of the University of Otago, New Zealand. A total of 165 participants were randomized to one of four intervention groups: habitual diet supplemented with 500 mL of either bovine milk, caprine milk, or ovine milk daily for 12 weeks; or a habitual diet with no additional milk (control) group to study the effects of sustained consumption of these milks on digestive comfort, nutrient intake, and metabolism among older women. Bovine milk powder was supplied by Miraka Ltd. (Taupo, New Zealand), caprine milk powder by NIG Nutritionals Ltd. (Auckland, New Zealand), and ovine milk by Spring Sheep Milk Co. (Hamilton, New Zealand). After a lead-in period of 2 weeks, participants consumed their assigned milk, attended clinic visits for measurements and biological sample collection and completed validated questionnaires over the course of 12 weeks.

At baseline and after 12 weeks of the intervention, a subgroup of participants from each milk group consumed a bolus dose (500 mL) of their assigned milk, had sequential blood samples taken and completed assessments to assess acute postprandial plasma amino acids, triglycerides, insulin, and appetite hormones in response to consuming the study milks.

The trial protocol has been prospectively registered with the Australia and New Zealand clinical trials Registry (ANZCTR) with registration number ACTRN12622001161718. Data collection commenced in January 2023 and concluded on the 27th of March 2024 and lab analyses have commenced.

### 2.2. Recruitment and Eligibility Criteria

A total of 165 healthy older women were recruited from the general population in Dunedin and Christchurch through a combination of online and community-based recruitment strategies. This included study posters put up around the university, local general practitioners, local hospitals, and local churches, newspaper advertisements, radio advertisements, community talks and presentations to older adult groups (University of the Third Age, Probus, Age Concern Otago, 60 plus), social media posts (Facebook, Instagram) and through word of mouth by Māori and other health nurses. All individuals who expressed an interest in the study were invited for screening and assessed for eligibility according to the inclusion and exclusion criteria listed below:Inclusion criteria:
Healthy, non-institutionalized women aged 60 to 80 years.Body mass index >18.5 or <40 kg/m^2^.Do not undertake structured exercise for more than 2 h per day.
Exclusion criteria:
Unable to give informed consent.Unable or unwilling to comply with the study procedures.Have taken antibiotics within 4 weeks of starting the study.Have taken certain prescribed medications or recreational drugs that could affect the gastrointestinal tract within 4 weeks of starting the study: opioids, non-steroidal anti-inflammatory drugs, laxatives, prebiotic, or probiotic supplements.Have medical history of gastrointestinal surgery or disorders (inflammatory bowel disease, ulcerative colitis, coeliac disease, Crohn’s disease), cardiorespiratory problems, uncontrolled diabetes mellitus, bleeding disorders, sleep disorders, psychiatric conditions (major depressive disorder, schizophrenia, bipolar disorder, post-traumatic stress disorder).Have alarm features associated with significant gastrointestinal or other disorders, such as burning pain in the epigastrium, which increases during the night and wakes the patient up; frequent vomiting; loss of appetite; lower gastrointestinal bleeding; odynophagia; dysphagia; palpable abdominal mass; lymphadenopathy; and jaundice.Experienced unintentional weight loss of ≥5% within the month of starting the study.Have dairy intolerance or ruminant milk allergy.Have a high habitual milk intake (≥500 mL ≥4 days per week).Malnutrition Screening Tool score of 2 or more points.Use tobacco, including cigarette smoking or other use of tobacco or nicotine-containing products.Excessive alcohol intake, i.e., >20g of pure alcohol (2 drinks)/d on average (>21 standard drinks a week).Screening blood biochemistries:▪HbA1c > 54 mmol/mol Hb (appropriate for older adults) [57].▪Blood biochemistry test results (Table A1) > 2 times the upper limit of normal.▪Hb < 120 g/L.
Non-exclusion criteria:

Cardiovascular disease, hypertension, diabetes mellitus, or depression that are well-controlled with medical intervention.

Out of the 165 participants enrolled in the study, 9 participants allocated to the milk groups consented to and completed the acute sub-study.

### 2.3. Participant Flow

A flow diagram of the study protocol is outlined in Figure 1. Participants attended the study clinic for one screening visit and three study visits (week −2, week 0 and week 12) in addition to completing daily and weekly questionnaires on a mobile application (app) developed for the study or on paper (Table A2). Participants collected their 4-week supply of milk powder at week 0, week 4 and week 8 and returned any unused milk powder at week 4, week 8 and week 12.

#### 2.3.1. Screening

Respondents who expressed interest in the study completed an online pre-screening questionnaire to evaluate their current health status and lifestyle habits. This questionnaire consisted of selected question domains adapted from the New South Wales Population Health Survey (NSW Population Health Survey Questionnaires, Methods, Results and Data Dictionaries for Adults, n.d.), covering areas for diabetes, smoking, alcohol consumption, and physical activity. Potentially eligible respondents were invited to attend a screening visit at the study clinic where they had the opportunity to ask questions about the study and their responses to screening questions were reviewed by a research assistant. Once informed consent was obtained, respondents had their anthropometric measurements (height, weight) taken and provided fasted blood samples (for screening blood biochemistries, Table A1) to determine their study eligibility.

#### 2.3.2. Main Study

Once participants’ blood chemistry was confirmed to meet study requirements, eligible individuals were formally enrolled, assigned a unique study identifier, and began their 2-week lead-in phase. Participants received links to relevant questionnaires and surveys (Table A2) along with instructions on how to complete them. They were given the option of completing the questionnaires via the study app or on paper.

One week prior to their baseline visit (week −1) and on the last week of the study (week 11), participants collected three-day diet records on three randomly assigned days (2 weekdays, 1 weekend day). They also tracked their physical activity and sleep for 7 days using an accelerometer (ActiGraph wGT3X-BT, Actigraph LLC, Pensacola, FL, USA). Participants underwent a dual-energy X-ray absorptiometry (DEXA) scan one week before their baseline and final study visits. Dunedin participants were scanned on the Lunar iDXA scanner (GE HealthCare, Madison, Wisconsin, USA) while Christchurch participants were scanned on the Lunar Prodigy scanner (GE HealthCare, Madison, Wisconsin, USA),

One day prior to their baseline and final study visits, participants collected stool samples using the OMNIgene GUT collection systems OMR205 and ME200 (DNA Genotek Inc., Ottawa, ON, Canada). They kept the tubes at room temperature until delivery to the clinics the following day. The tubes were filled with proprietary stabilization solutions designed for preserving DNA, RNA and metabolome at room temperature for 30, 10, and 7 days, respectively. Additionally, participants consumed a standardized meal provided to them for their evening meal before their baseline and final study visits, and fasted thereafter for 10 h. The standardized meal consisted of a Plantry Foods Lasagne (350 g, Goodman Fielder, New South Wales, Australia) or a Weight Watchers Mushroom and Pumpkin Risotto (320 g, as a gluten-free option, WW International Inc., New York, NY, USA) and an Alpro Soya Chocolate Dessert (125 g, Alpro, Ghent, Belgium). The meal was provided to standardize nutrient intake among participants and mimimize variability in blood biomarkers because of dietary factors apart from the study intervention [58].

At their baseline and final study visits, participants had their blood pressure, fasted blood samples and anthropometric measurements (height, weight, waist circumference) taken. They also completed functional tests such as a timed walk test and a hand grip strength test. At baseline, participants filled out the Economic Living Standard Index Short Form (ELSISF) to measure their economic standard of living, i.e., the material aspect of wellbeing reflected in their consumption habits and personal possessions [59]. Data collected will be used to assess their socioeconomic status and identify any important issues that may confound study data.

Full details of study outcomes and measurements are provided in Section 3.

#### 2.3.3. Acute Sub-Study

Before the baseline visits, all participants allocated into milk groups were invited to take part in the acute sub-study. Those who consented consumed a bolus dose (500 mL) of their allocated milk and had sequential blood samples drawn for acute assessments at 0, 60, 120, 180, 240, and 300 min during their baseline and final visits. They also filled out a 100 mm Visual Analog Score (VAS) over the five hours to measure gastrointestinal symptoms and appetite parameters.

### 2.4. Randomization and Blinding

Participants were randomly assigned to one of four groups: bovine milk, caprine milk, ovine milk, and control (no milk) in a 1:1:1:1 ratio with a pre-specified computer-generated random block randomization list prepared by the study statistician. Block sizes of eight were used without any stratification. To mimize bias, participant allocation was carried out by the principal investigator, who supplied the allocation for each participant to the research team a week before the participants were scheduled to come in for their baseline visits and all data analysis will be performed by blinded researchers.

Study participants were not informed about their milk intervention, but no attempt was made to mask the flavor of the milks. Researchers assessing study outcomes and conducting data analysis will remain blinded to participation allocation until the completion of statistical analyses for the primary and key secondary outcomes.

### 2.5. Intervention

Participants in the milk groups were given a 4-week supply of their assigned milk powder at baseline (week 0), week 4 and week 8. They were asked to maintain their usual diet and consume one serving of their assigned milk twice daily, with breakfast and lunch, over the 12-week intervention period. Participants reconstituted their assigned milk powder by weighing out their daily portion (as detailed in Table 1) and dissolving it in lukewarm water before making up the milk to 500 mL and mixing it thoroughly. Once mixed, the milk was refrigerated. The following day, they would have half with breakfast and the other half with lunch. The daily portions were calculated to match the nutrient composition of fresh milk while providing the same volume of study milk to all participants in milk groups. Depending on the type of milk, the intervention would add 9–14 g of protein to each meal, totalling 18–29 g of protein each day. Participants were asked to consume their milk at breakfast and lunch to increase protein intakes during these meals, as protein intakes are typically low for these meals [60,61]. Participants in the control group were asked to follow their usual diet for 12 weeks with no restrictions on their milk or dairy intake.

### 2.6. Attrition and Compliance/Adherence

To reduce attrition, strategies such as creating a welcoming environment for the participants, flexibility in scheduling clinic visits (±2 days), sending out email reminders the day prior to each scheduled visit and providing financial remuneration to those taking part in the study were employed. For the latter, all possible participants who attended the screening clinic received a $20 supermarket voucher, and those participating in the study received a $100 supermarket voucher after the baseline visit and an additional $100 upon completion of the study.

To improve compliance, participants in the milk groups were given Vital Zing Caramel Milk Drops (Vital Zing, Auckland, New Zealand) to increase the palatability of the milks. Fortnightly phone calls to the participants were also made by study personnel to discuss adherence and troubleshoot any difficulties encountered. Participants struggling to adhere to the interventions were offered support in the form of counseling from a dietetics student, supervised by a registered dietitian, to help them improve compliance. To assess compliance, participants in the milk groups were asked to fill out a daily compliance diary, reminded not to share their milk powder with anyone else and asked to return any unused milk powder during their week 4, 8 and 12 clinic visits. To quantify milk consumption, the unused milk powder was weighed and the amount deducted from the total provided, with the understanding that errors or spills may have occurred.

### 2.7. Participation and Withdrawal from the Study

Participation in the study was voluntary, and participants had the right to withdraw from the study at any time. The principal investigator had the right to discontinue a participant from the study if they became ineligible, they experienced significant adverse events such as allergic reactions, there was significant protocol deviation or non-compliance with study requirements, or they withdrew their consent.

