### 2.8. Risk and Adverse Events

While no significant adverse events have been reported for studies of this nature, and the study and the intervention are low risk, participants might experience events such as gastrointestinal discomfort and weight gain caused by the addition of milk, discomfort caused by venepuncture, and low blood sugar due to fasting. Participants were provided information about these risks before they provided informed consent for the study. Management actions were put in place such as referral to a dietetics student, supervised by a registered dietitian, for dietary advice and support, the engagement of trained phlebotomists, and the provision of snacks and beverages after blood draws.

Adverse events were monitored and recorded by the research team, and the research team assessed and managed the condition. In the event of significant adverse events, the participant would be referred to the study clinician for assessment and management plan, and the event recorded in the case report form.

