### 4.2. Statistical Analysis

All data collected will be analyzed for both intention-to-treat (ITT) and per-protocol (PP) populations. The ITT population will include all randomized participants who have taken at least one serving of their assigned study milk whereas the PP population will include all randomized participants who have completed the study and have complied with at least 80% of the intervention without major protocol violations. All analyses will be undertaken using SPSS v28 (IBM, New York, NY, USA) or R version 4.3.3 (The R Foundation, Vienna, Austria) by blinded researchers with guidance from an independent biostatistician and statistical significance will be set at a two-tailed *p* value of less than 0.05.

All study outcomes will be summarized using descriptive statistics such as mean, standard deviation, median, range, frequency and percentage according to data type. Univariate and covariate analyses will be performed to evaluate and compare the changes for patient reported outcomes, blood biomarkers, blood pressure, anthropometric measurements, body composition, and functional tests. Chi square tests and logistic regression will be used to analyze categorical data. One-way ANOVA and general linear mixed models with ‘participant’ as a random factor, ‘study timepoint’ and ‘study allocation’ as fixed factors will be used to analyze continuous data. Further models incorporating baseline levels and other potential confounding or explanatory variables may also be used to explore the outcomes and the relationships between specific outcomes.

For stool microbiome analysis, the relative abundance of bacterial taxa, gene abundance, and alpha and beta-diversities will be compared. If these data do not meet the assumptions for parametric testing, the non-parametric permutation ANOVA known as ANCOMBC [99] will be used to analyze microbiome data to account for the high dimensionality, non-normality, and phylogenetic structure of the data.

A priori planned comparisons of within-group and between-group changes will focus on the changes from baseline to the week 12 endpoint.

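### Allowing women to be discontinued from the study for non-compliance may selectively lose milk-arm women with discomfort and bias the week-12 comfort contrast in favor of milk

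*Protocol article*

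**What the plan says.** Section 2.7 states that "The principal investigator had the right to discontinue a participant from the study if they became ineligible", and lists among the further grounds that "there was significant protocol deviation or non-compliance with study requirements, or they withdrew their consent". It gives no threshold for non-compliance, does not separate stopping the milk from leaving the study, and does not say whether outcome collection continues afterwards.

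On who can be found non-compliant with the product, Section 2.6 says "To assess compliance, participants in the milk groups were asked to fill out a daily compliance diary", and returned powder was weighed in those groups. The control group was "asked to follow their usual diet for 12 weeks with no restrictions on their milk or dairy intake" (Section 2.5).

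Section 2.8 foresees that "participants might experience events such as gastrointestinal discomfort and weight gain caused by the addition of milk". Section 3.1.1 makes the GSRS abdominal pain domain, baseline to week 12, the primary outcome and has it completed weekly from enrolment.

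Section 4.2 keeps in the ITT set randomized women who took at least one serving, and restricts the PP set to completers who "have complied with at least 80% of the intervention without major protocol violations". It names one-way ANOVA and a mixed model with participant as a random factor, and focuses planned comparisons on change to week 12. Section 2.4 has the principal investigator carrying out allocation, so the holder of the discretion in Section 2.7 knows the arm.

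**The concern.** In this trial, not drinking the milk can itself be a sign of the outcome. A woman whose abdomen hurts on the product may drink less of it, be judged non-compliant and leave the study before week 12. The control arm has no product and so no matching route. Loss that depends on the outcome and differs by arm biases the comparison, here toward better comfort on milk. If one milk is less well tolerated than the others, the same mechanism would shrink the between-milk difference that the trial sets out to study.

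Membership of the ITT set does not cure this. It keeps the woman in the denominator but does not create a week-12 score. A one-way ANOVA of change to week 12 drops anyone without that score, so under that method the ITT result can approach a completers' result.

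**Working it through.** **The plan's own figures (Section 4.1).**
- Attrition step: 34 / (1 − 0.15) = 40 per group. This reproduces.
- Effect size 0.7, two-sided 5%, 80% power: 33 per group by the normal approximation; 33.02, rounded up to 34, by the t-test. This reproduces.
- The 34 per group for a 0.6 difference cannot be checked independently, because the SD is not printed. Solving back: SD = 0.6 × √(34/2) / (1.960 + 0.842) = 0.88.

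The discontinuation rule changes none of these. Its effect is a possible bias.

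**Size of the bias.** Let d be the share of a milk arm lost through this route and g the excess GSRS worsening, at week 12, of those lost over those who stay. The full-arm mean change is (1 − d) × m + d × (m + g) = m + d × g, where m is the mean change in those who stay. A completers-only analysis reports m, so it is too favorable by d × g. Control is assumed to have no such loss. Neither d nor g is in the document. The 15% is the article's predicted attrition from all causes, used here as a high value for d.

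| d | g = 0.6 | g = 1.2 | g = 2.0 |
|---|---|---|---|
| 5% | 0.03 (5% of 0.6) | 0.06 (10%) | 0.10 (17%) |
| 10% | 0.06 (10%) | 0.12 (20%) | 0.20 (33%) |
| 15% | 0.09 (15%) | 0.18 (30%) | 0.30 (50%) |

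**What this does to a true worsening of 0.6.** The apparent difference is e = 0.6 − d × g. With 34 evaluable per group and SD 0.883, the standard error is 0.883 × √(2/34) = 0.214, and power ≈ Φ(e / 0.214 − 1.96).
- d = 5%, g = 0.6: e = 0.57, power 76%.
- d = 15%, g = 0.6: e = 0.51, power 66%.
- d = 15%, g = 1.2: e = 0.42, power 50%.
- d = 15%, g = 2.0: e = 0.30, power 29%.

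Without the bias the figure is 80%.

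**The case against.** The case on the other side is substantial.

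- **The clause is a right, not an automatic removal.** Section 2.6 describes phone calls and dietetic counseling as the response to poor adherence. A PP set defined by 80% compliance makes sense only if some non-compliers stay in the wider set. This stands, and it points to a small d.
- **Discomfort is not the only cause.** Flavor drops were supplied "to increase the palatability of the milks", so taste was foreseen as a barrier, and Section 2.2 excludes women with dairy intolerance or milk allergy at entry. A reader might infer that the rule mainly removes women who stopped because of discomfort. The document gives no counts or reasons and does not support that.
- **Study requirements bind controls too**, through visits, questionnaires, diet records and samples. This stands; only the product part of compliance is specific to the milk arms.
- **Earlier scores can be used.** The GSRS is weekly and a mixed model is named. A reader might infer that the week-12 result comes only from women who tolerate milk. That is close to true of the PP set or of a completers-only ANOVA, not of a mixed model using all weeks. The reply is partial: Section 4.2 does not say that the intermediate weeks enter the model, and the model is valid only if data are missing at random. A woman who cuts back before leaving may record improving scores that understate her discomfort on milk.
- **The excess may fade.** If discomfort resolves once milk stops, g at week 12 is small in a comparison by randomized arm. This is why the range must reach down toward zero.
- **Missing-data handling may sit in an unseen analysis plan.** That is so, and its absence is not the point. The point is a stated conduct rule combined with a stated week-12 focus; no analysis plan can recover scores that were never collected.

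**Conclusion.** The concern holds as a risk, not as a demonstrated bias. Sections 2.7 and 4.2 together permit loss that is related to the primary outcome and falls more on the milk arms, decided by someone who knows the allocation. The direction, if it occurs, favors milk.

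The magnitude cannot be read from the document. Under the assumptions above, a completers-only contrast shifts by about 0.03 to 0.30 points, 5% to 50% of the 0.6 minimal important difference. The top of that range is a worst case: it assigns all of the predicted all-cause attrition to women with discomfort, gives control no such loss and ignores every score before exit. That discontinued women have no week-12 score is itself an inference, since Section 2.7 is silent on later collection. The point merits action because the remedy is cheap and still available, not because a large bias has been shown.

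**What to change.** Data collection ended in March 2024, so the remedy is analytic. Section 2.4 keeps analysts blinded until the primary and key secondary analyses are complete. The following should be fixed before unblinding:

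1. Reconcile Sections 2.7 and 4.2: state whether outcome data were retained, and will be analyzed, after a woman was found non-compliant or discontinued.
2. Make the primary GSRS analysis a mixed model using every weekly score collected from every randomized woman in her randomized arm, including any collected after she stopped the milk, rather than a completers-only week-12 ANOVA.
3. Report discontinuations by arm and reason, separating investigator discontinuation for non-compliance, gastrointestinal reasons and other reasons.
4. Add a delta-type missing-not-at-random sensitivity analysis. Assume women who left for gastrointestinal reasons are worse by a range of values, for example 0 to 2 points, and vary non-compliance of other or unknown cause separately. Counting every non-compliance exit as worsened comfort would load the analysis against milk, because product non-compliance cannot occur in control.

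The cost is some analysis-plan wording, one sensitivity analysis and one table, provided that reasons for discontinuation were recorded. The milk arms may look less favorable. No rule on when milk should be stopped is proposed.
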